**Fig. 1 Fig1:**
[figure not shown]
Study flow chart

**Table 1 Tab1:** SPIRIT figure of study structure

	Study period					
Timepoint	Enrolment	Implantation	Trial	3 months	6 months	12 months
Enrolment:						
Eligibility screening	X					
Informed consent	X					
Randomization	X					
Intervention:						
Active burst neuromodulation		X	X	X	X	X
Passive burst neuromodulation		X	X	X	X	X
Open-label phase		In case of LOE	In case of LOE	In case of LOE	In case of LOE	X
Assessments:						
PCS	X		X	X	X	X
NRS	X		X	X	X	X
ODI	X		X	X	X	X
PainDETECT	X		X	X	X	X
PVAQ	X		X	X	X	X
HADS	X		X	X	X	X
PGIC	X		X	X	X	X
CPH/CPM				X	X	X

*LOE* loss of effect

Recording of adverse events (AE) and serious adverse events (SAE) is done through the CASTOR data management system.

### Data management

Patients are given an ID number upon entering the study. The list of ID numbers and corresponding patient details is accessible only to specific members of the research staff. The anonymized ID numbers are logged in the password-protected CASTOR data management system, where study records are kept.

### Sample size calculation

This study follows a non-inferiority setup based on the primary outcome measure, the PCS. The non-inferiority limit of 7 points on the PCS scale (13.46%) was defined based on an estimation of the clinically meaningful score of PCS scores established on experience with this test at the main research centre. Previous literature investigating the clinically meaningful difference of the PCS scale estimates that this lies at around 44% [51]. However, as this study was performed in patients with subacute pain after whiplash injury, the decision was made to lower the non-inferiority limit for patients with PSPS Type 2, a chronic debilitating condition with neuropathic components.

In order to calculate group size, an estimation of the expected standard deviation (SD) was based on previous literature for FBSS patients with neuromodulation to be 12.04 points on the PCS scale [4]. In combination with a non-inferiority limit of 7 points, 80% power and 5% significance level, this results in a group size of 37 patients per group or 74 patients total. Compensating for a drop-out rate of 20% (including failed initial trials), we arrive at 92.5 patients. However, this is rounded to 94 patients in order to ensure even group size of 47 patients per group.

### Statistical analysis

All main analyses will be performed according to the intention-to-treat principle. Hence, all patients who do not show sufficient pain reduction in the first phase will still be considered for the analyses. In addition, an exploratory per protocol analysis will be performed on those that do show sufficient benefit in the first phase.

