### Study procedure

 Following inclusion and consent, patients are randomized into two groups: passive burst SCS or active burst SCS. Randomization is performed by local study staff using Castor study management software. Patients are stratified per group and per center for PCS rate (two groups of 20-35 and 35-52), gender and pain location.

Procedures in this study do not deviate from standard neuromodulation care for PSPS Type 2 patients. First, a trial period occurs where patients are implanted with either two Abbott Octrodes or two Boston Scientific Infinion leads in the dorsalepidural space; during the procedure paresthesia testing is performed to achieve maximum overlap with the pain area of the patient. During this trial period, patients are stimulated by an external pulse generator. Stimulation settings are set by clinical programmers provided by Abbott and Boston Scientific, who individually assess optimal burst stimulation parameters for every individual participating patient. Due to the subsequent nature of the study, patients cannot be blinded. Following a test phase of 2 weeks and a minimal pain reduction of 50%, patients are implanted with an internal IPG (Proclaim 5/XR (Abbott Laboratories) or Waverwriter Alpha (Boston Scientific)). When pain reduction is less than 50%, the trial is expanded by 1 week, and other (non-burst) waveforms possible with the implanted system can be tried, with the aim to induce pain relief. These patients, with at least 50% pain relief, will remain in the study and complete long-term follow up questionnaires.

Data regarding pain state and mental attitude towards pain are collected at baseline, after trial, 1 month, 3 months, 6 months and 12 months following implantation. Patients will electronically complete the Pain Catastrophizing Scale (PCS) [38], Numeric Pain Rating Scale (NRS), Patient Vigilance and Awareness Questionnaire (PVAQ) [40, 41], Hospital Anxiety and Depression Scale (HADS) [42, 43], Quality of Life (EQ-5D) [44–46], Oswestery Disability Index (ODI) [47], Patient Global Impression of Change (PGIC) [48] and painDETECT [49, 50] questionnaires using the CASTOR data collection system. Additionally, use of pain medication alongside neuromodulation is recorded at every follow-up contact, as well as the mean charge per second (CpS) and mean charge per hour (CpH) as used by the stimulation apparatus in order to gain insight into electrical consumption.

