### Primary study parameters

Between-group differences in mean PCS scores at 6 months will be computed including the one-sided 95% confidence interval. The upper bound of the difference will be compared to the non-inferiority margin of 7 points. If the margin lies in the 95% confidence interval, the null-hypothesis that active recharge is not inferior to passive recharge cannot be rejected.

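### Patients who never pass the trial stimulation are promised a place in the intention-to-treat analysis, but the article defines no 6-month PCS for them and budgets them as drop-out

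*Protocol article*

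**What the plan says.** Under Study procedure, randomisation follows consent and comes before the trial stimulation. Permanent implantation requires at least 50% pain reduction after two weeks. Patients below that get one more week, in which non-burst waveforms may be tried. The article then says: "These patients, with at least 50% pain relief, will remain in the study and complete long-term follow up questionnaires". Assessments are scheduled at "baseline, after trial, 1 month, 3 months, 6 months and 12 months following implantation", and the hypothesis in the Background is also set at six months from implantation.

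Under Sample size calculation: "Compensating for a drop-out rate of 20% (including failed initial trials), we arrive at 92.5 patients".

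Under Statistical analysis, the main analyses are intention-to-treat, with the consequence that "Hence, all patients who do not show sufficient pain reduction in the first phase will still be considered for the analyses". A per-protocol analysis of those with enough first-phase benefit is exploratory.

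Under Primary study parameters: "Between-group differences in mean PCS scores at 6 months will be computed including the one-sided 95% confidence interval". The upper bound is compared with 7 points, and the question is whether active recharge is inferior to passive.

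Study procedure and Table 1 also allow early entry to the open-label phase for insufficient relief, even during the initial trial.

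**The concern.** Passing the trial stimulation is an outcome of the allocated system, so a comparison restricted to those who pass is no longer the randomised comparison. The Statistical analysis section says this will not happen, but the follow-up and sample-size text point to data in which it would. A patient who never reaches 50% relief is not among those said to remain, is already counted as a loss, and has no permanent implantation from which six months can be counted.

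In a non-inferiority trial this can work quietly: if the tested arm loses more of its poor responders, part of a true disadvantage never enters the mean. The Background itself allows that the two waveforms may differ in efficacy, so equal failure rates cannot be taken for granted.

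**Working it through.** **1. The plan's own figure.** Inputs from Sample size calculation: margin 7, SD 12.04, power 80%, significance level 5%. The level is taken as one-sided, to match the one-sided interval in Primary study parameters.

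n per group = 2 × (1.645 + 0.842)² × 12.04² / 7² = 36.6, so 37 per group and 74 in total. Then 74 / 0.80 = 92.5, rounded to 94 (47 per group). The stated size reproduces and the arithmetic is not at fault.

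**2. What the inflation implies.** 94 × 0.80 = 75.2 patients analysed, against 74 needed. Up to 94 × 0.20 = 18.8, about 19 patients, are expected to give no primary outcome. Failed trials belong in that allowance only if they yield no 6-month PCS.

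**3. The sections side by side.**

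| Patient after the trial stimulation | Followed up? | 6-month date? | Analysed? |
|---|---|---|---|
| At least 50% relief at two weeks | yes | yes | yes |
| Below 50%, then at least 50% on another waveform | yes | yes | yes |
| Never reaches 50% | not among those said to remain; budgeted as drop-out | none from permanent implantation | yes, by the intention-to-treat statement |

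The third row is the conflict.

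**4. Size and direction of the possible bias.** Let f be the share of an arm that never passes, R the mean PCS of those who pass, and D the number of points by which failures score worse (same D in both arms). The all-randomised mean is (1 − f)R + f(R + D) = R + fD. The active minus passive difference is therefore (R_A − R_P) + (f_A − f_P)D. A passers-only comparison shows R_A − R_P and hides (f_A − f_P)D. The article gives neither f nor D, so these are assumptions:

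| Failures, active vs passive | D = 5 | D = 10 | D = 15 |
|---|---|---|---|
| 20% vs 20% | 0 | 0 | 0 |
| 25% vs 15% | 0.5 | 1.0 | 1.5 |
| 30% vs 10% | 1.0 | 2.0 | 3.0 |

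If passive fails more, the same amounts apply with the opposite sign.

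**5. What this does to the error rate.** SE = 12.04 × √(2/37) = 2.80. Let the true all-randomised difference equal the margin. The chance of declaring non-inferiority is then Φ(hidden/2.80 − 1.645), which is 5% with nothing hidden. With active failing more it is Φ(−1.47) = 7% for 0.5 points, Φ(−0.93) = 18% for 2 points and Φ(−0.57) = 28% for 3 points.

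**6. Power if failures are measured.** Assume 20% fail in each arm. The mixture SD is √(12.04² + 0.2 × 0.8 × D²), and power at 47 per arm is Φ(7 / (SD × √(2/47)) − 1.645).

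| D | SD | Power at 47 per arm | Evaluable n per arm for 80% |
|---|---|---|---|
| 0 | 12.04 | 88% | 37 |
| 5 | 12.2 | 87% | 38 |
| 10 | 12.7 | 85% | 41 |
| 15 | 13.5 | 81% | 46 |

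The room left for other losses is 47 − 38 = 9, 47 − 41 = 6 or 47 − 46 = 1 per arm for D = 5, 10 or 15.

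**The case against.** Several points on the other side stand and limit the claim.

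- **Exit is not stated outright.** A reader might infer that the article removes failures from follow-up. It says only who remains, and the rest follows by implication from that sentence and the drop-out allowance. The provision for early open-label entry, even from the initial trial, could be read as keeping some of them. That provision concerns waveforms of an implanted system, though, and gives no schedule for a patient without one.
- **First phase may mean the two-week burst test.** Patients rescued by another waveform do stay and can be analysed as randomised. It would therefore be wrong to call the analysed set burst responders. This reading still does not cover patients who never reach 50%, and the intention-to-treat sentence speaks of all patients.
- **Implantation may mean lead placement.** Table 1 puts it before the trial stimulation, and the Background speaks of the initial implantation. A date would then exist for everyone who received leads. The abstract, however, places follow-up after permanent implantation, and on either reading the article does not say that failures are followed to that date.
- **An unseen analysis plan may handle missing data.** Inflating for loss does not contradict intention-to-treat, and baseline and after-trial PCS are scheduled, so a model-based all-randomised analysis is possible. It would be too strong to say that none can be done. But with no failure observed at six months, such an analysis must borrow from implanted patients or from a score taken a few weeks after lead placement. An analysis plan cannot supply data that were not collected.
- **The bias has no fixed direction.** A reader might infer that losing failures always helps non-inferiority. The test is of active against passive, so this is true only if active fails more.

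**Conclusion.** The conflict stands. The article promises to analyse all first-phase failures, yet for those who never pass it defines no 6-month PCS and counts them as drop-out. As planned, the primary mean would come from patients who passed the trial on any waveform of the allocated system.

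Under the assumed failure splits and deficits, about 0.5 to 3 of the 7 margin points are hidden. This favours non-inferiority if active fails more and works against it if passive does. With equal rates and equal deficits there is no bias, but the contradiction remains. The false-positive rates of 7% to 28% illustrate those assumptions with active failing more. They are not estimates for this trial, since the article gives no failure rates by arm and says only that its 20% allowance includes failed trials.

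**What to change.** 1. Reconcile Study procedure (who remains, and early open-label entry), Sample size calculation and Statistical analysis, so that they agree on what happens to a patient who never reaches 50% relief.
2. Keep sending the electronic PCS to non-implanted randomised patients at a defined equivalent date, for example six months after the end of the trial stimulation or the matching time from randomisation. Analyse them in their randomised arm. Implanted patients can keep their present schedule; re-timing the endpoint for everyone would change the stated objective more than is needed.
3. Take failed trials out of the drop-out allowance, so that it covers missing questionnaires only.
4. If these data will not be collected, describe the primary analysis as one of implanted patients and do not call it intention-to-treat.

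The cost is an amendment and a few electronic questionnaires for at most about 19 patients. The SD may rise: with all 47 per arm analysed, power is about 81% to 87% if 20% fail and are 5 to 15 points worse, with little room for other losses at the upper end. The first patient was included in February 2022, so the 6-month PCS of failures before the amendment may not be recoverable. Their number by arm should be reported.

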### Primary study parameters

Between-group differences in mean PCS scores at 6 months will be computed including the one-sided 95% confidence interval. The upper bound of the difference will be compared to the non-inferiority margin of 7 points. If the margin lies in the 95% confidence interval, the null-hypothesis that active recharge is not inferior to passive recharge cannot be rejected.

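### The primary comparison uses the 6-month PCS alone, so on its natural reading patients without that score fall out of the intention-to-treat result and their earlier PCS goes unused

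*Protocol article*

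**What the plan says.** All references are to the protocol article.

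- **Primary study parameters:** "Between-group differences in mean PCS scores at 6 months will be computed including the one-sided 95% confidence interval". The decision rule follows: "The upper bound of the difference will be compared to the non-inferiority margin of 7 points". No covariate, repeated-measures model or missing-data rule is named.
- **Statistical analysis:** "All main analyses will be performed according to the intention-to-treat principle". The section adds that patients without enough pain reduction in the first phase stay in consideration.
- **Sample size calculation:** "Compensating for a drop-out rate of 20% (including failed initial trials), we arrive at 92.5 patients".
- **Study procedure:** PCS and the other questionnaires are "collected at baseline, after trial, 1 month, 3 months, 6 months and 12 months following implantation". Implantation follows a trial with at least 50% pain reduction. Patients who reach 50% only in the extended trial week also stay in the study and complete the long-term questionnaires. Nothing is said about follow-up of patients who never reach 50%.
- **Table 1** lists PCS at enrolment, trial, 3, 6 and 12 months, with no 1-month column.

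**The concern.** A difference of two observed means at month 6 can use only patients who have a month-6 score. A patient who fails the stimulation trial and is not implanted has no visit 6 months after implantation, and an implanted patient who leaves earlier has no month-6 score either. The label is intention-to-treat, but the stated estimator behaves as a complete-case comparison.

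Two things are at stake. First, PCS already collected from these patients is not used, which costs precision. Second, a complete-case mean is free of bias only if loss is unrelated to PCS. Part of the loss here is tied to response by design, because a failed trial means less than 50% pain relief. The study is also unblinded, and the alternative waveforms depend on the allocated system. In a non-inferiority trial, any selection that pulls the two means together favours the claim.

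**Working it through.** **Inputs.** From Sample size calculation: margin 7, SD 12.04, 80% power, 5% significance, 20% loss, 47 per group. One-sidedness comes from Primary study parameters. The article gives neither the correlation r between an earlier post-baseline PCS and the 6-month PCS nor a loss mechanism. Both are assumed below: r from 0.3 to 0.8, and several mechanisms.

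**1. The plan's own figure.** n per group = 2(1.645 + 0.842)² × 12.04² / 7² = 2 × 6.185 × 144.96 / 49 = 36.6, so 37, as stated ("this results in a group size of 37 patients per group or 74 patients total"). Then 74 / 0.80 = 92.5, raised to 94, or 47 per group. After 20% loss, 47 × 0.80 = 37.6 per group remain. Dividing by 0.80 gives lost patients, failed trials included, no weight in the primary result.

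**2. Precision under random loss.** Complete-case variance is 2 × 144.96 / 37.6 = 7.71, so SE = 2.78 and power = Φ(7/2.78 − 1.645) ≈ 0.81. If one earlier post-baseline score is used for patients without a 6-month score, the variance is 2 × SD² × [(1 − r²)/37.6 + r²/47]. That is 7.71 × (1 − 0.2r²):

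| r | Variance saved | SE | Power |
|---|---|---|---|
| 0.3 | 1.8% | 2.75 | 0.82 |
| 0.5 | 5.0% | 2.71 | 0.83 |
| 0.7 | 9.8% | 2.64 | 0.84 |
| 0.8 | 12.8% | 2.59 | 0.85 |

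**3. False non-inferiority when the true active-minus-passive difference is 7 (nominal 5%).** Simulation: 47 per arm, 6,000 runs per setting, r = 0.5 or 0.7, loss generated from the trial-end PCS. Each result can be checked with Φ((7 − D)/SE − 1.645), where D is the average complete-case difference.

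- Random loss: about 5%.
- Same rule in both arms, high scorers more likely lost: 6.6% to 11%. At r = 0.7 with 16% lost on passive and 24% on active, D = 6.44 and SE = 2.70, so Φ(0.21 − 1.645) ≈ 7.5% (simulated 7.7%). With a steeper rule (14% and 26% lost), D = 5.85 and SE = 2.61, so Φ(0.44 − 1.645) ≈ 11.4% (simulated 11.4%). Average loss is about 20% in both.
- Same rule in both arms, low scorers more likely lost: 6.4% to 7.4%.
- High scorers lost in the active arm only (10% and 33% missing): 19% to 30%. At r = 0.7, D = 3.96 and SE = 2.75, so Φ(1.11 − 1.645) ≈ 29.5% (simulated 30.2%).

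A second simulation, with several visits, correlations of 0.5 to 0.8 and 4,000 runs, gave 6-9% under a common rule (20-28% versus 26-39% lost) and 17-27% under active-arm-only loss.

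An estimator that also uses the trial-end PCS stayed at 4.4% to 5.5% in every setting of the first simulation. This is by construction, because loss was generated from that observed score. It shows what the method can repair, not that this trial's loss is of that kind.

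**The case against.** **Exclusion is not stated.** Nowhere does the article say that patients without a 6-month PCS are left out. A repeated-measures contrast or an imputed analysis would also yield a difference in means at 6 months, and missing-data handling may sit in a full protocol or SAP not shown here. This stands as a limit: complete-case handling is a reading. It is the natural one, because the sample-size inflation gives lost patients no weight and the text names no model. It also conflicts with the statement that patients without first-phase benefit remain in the analysis.

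**Planned power is not damaged.** This stands. Under random loss the inflation to 47 per group leaves about 81% power. The cost is forgone efficiency, not a shortfall. Baseline PCS would gain more (simulated power 0.89 at r = 0.5 and 0.97 at r = 0.7).

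**A reader might infer that false non-inferiority will reach 17-30%.** The documents do not support that. It needs high scorers to leave the active arm only, which no section suggests. The 50% rule applies to both arms and concerns pain, not PCS. If high scorers left only the passive arm, the passive mean would fall, the observed difference would widen and the test would be conservative.

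**A reader might also infer that every lost patient has unused scores at trial end, 1 and 3 months.** That is wrong for failed-trial patients, who have at most baseline and trial-end PCS.

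**The remedy leans on missing-at-random.** For never-implanted patients the model would project month-6 PCS from a single post-baseline score, using the course of implanted responders. This is a serious assumption and is why the fix needs a sensitivity analysis. It does not make the complete-case comparison safer, since that requires loss unrelated even to the observed scores.

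**Conclusion.** The point holds in moderate form. As written, the primary estimator works as a complete-case comparison under an intention-to-treat label and leaves collected PCS unused. Under random loss the error rate and planned power are kept, and about 2-13% of variance (1-5 power points) is forgone. If loss depends on earlier PCS by a common rule and the true difference is 7, false non-inferiority is about 6-11% instead of 5%. Arm-specific loss could make it much higher or conservative, and the documents do not indicate which. These sizes rest on assumed correlations (0.3 to 0.8 for precision; 0.5 to 0.8 across the simulations) and assumed loss mechanisms. Separately from any simulation, Study procedure, Sample size calculation and Statistical analysis do not agree on how a failed-trial patient enters the primary result.

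**What to change.** 1. Make the primary estimate the month-6 active-minus-passive contrast from a likelihood-based repeated-measures model (treatment by visit, unstructured covariance) on all PCS collected up to month 6 in all randomised patients. Compare its one-sided 95% upper bound with 7. Confirm whether the 1-month visit exists, since the text and Table 1 differ.
2. Because missing-at-random is a strong assumption for never-implanted patients, add a sensitivity analysis that imputes missing month-6 scores and adds a penalty to the active-arm values, rising to the 7-point margin. With 20% of the active arm missing, the full penalty moves the difference by 0.20 × 7 = 1.4 points. Report whether the conclusion survives.
3. Keep the simple difference in observed means as a further sensitivity analysis.
4. Reconcile Study procedure, Sample size calculation and Statistical analysis on whether failed-trial patients provide a 6-month PCS and, if so, from which date it is counted.

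Items 1 to 3 cost wording and standard software, with no new patients, visits or data. Item 4 is also wording, unless the answer is that these patients are to be followed, in which case their questionnaires must be scheduled.
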